### Biological outcomes

Insulin resistance and inflammation are the primary biomarker outcomes [10]. Insulin resistance is gauged by fasting plasma insulin and glucose levels, and the HOMA-IR index (fasting plasma insulin x fasting plasma glucose/22.5) [12]. Average 24 h circulating glucose levels were assessed by measures of HbA1c. Adipose tissue inflammation and insulin resistance are gauged by measuring the adipokines, adiponectin and leptin [42]. Systemic inflammation is gauged by levels of CRP (assayed in a multiplex panel with ICAM-1, VCAM1, and SAA – also markers of inflammation in insulin resistant subjects), [13, 43] IL-6, TNFα, and IL-10 (assayed in a multiplex panel with INFγ, IL-1β, IL-8, and IL-12p70 – also markers of inflammation in insulin resistant subjects), and MCP-1. IGF-1 axis is assessed measuring plasma IGF-1 and IGFBP - 3 levels. Impaired lipid metabolism is assessed by lipid panel measures of total, HDL and LDL cholesterol and triglycerides. Oxidative stress is assessed by urinary markers 8-oxo-dG and F2-isoprostanes [9, 44].

Anthropometric measures were taken in duplicate at the clinic visit. Height was measured without shoes using a stadiometer. Weight was measured without shoes using a bariatric digital scale, and waist circumference was measured along the midaxillary line using a flexible, non-stretchable measuring tape. Blood pressure was measured 3 times with 1 min between readings. A 4th measure was taken if two of three previous readings were > 5 mmHg different.

### Behavioral outcomes

Objective PA and sedentary behavior was measured by participants wearing a GT3X+ ActiGraph accelerometer (ActiGraph, LLC; Pensacola, FL) on the hip. Raw accelerometer data at 30 Hz is collected on 3 axes. Actigraph GT3X+ data are aggregated to the minute level using the low frequency extension. Participants wore the device for waking hours. During analysis, non-wear time is excluded using the validated Choi algorithm in Actilife 6 that clarifies invalid data as 90 consecutive minutes of zero counts with a 2 min tolerance and a 30 min small window to detect artificial movement [45]. The hip worn PA variables are created from collected accelerometer data employing traditional accelerometer count per minute (cpm) cut offs (e.g. moderate-vigorous PA 1952+; light intensity PA 100–1951+; and sedentary < 100) [46, 47], to be able to compare results to previous studies using these methods. However, we will also employ new machine learning techniques to classify specific behaviors related to built environments [48, 49]. These include walking/running, biking, sitting, standing still, standing moving, and sitting in vehicle. A random forest algorithm has been developed and tested by our group using a 10-fold cross validation on a training set with performance at 90% accuracy [50].

Objective sleep was measured by participants wearing a GT3X+ ActiGraph (ActiGraph, LLC; Pensacola, FL) on the non-dominant wrist for 24 h. Raw accelerometer data at 30 Hz is collected on 3 axes. Non-wear time is removed after being classified by 60 min of consecutive zeros on the vector magnitude [45]. Sleep duration and quality will be scored by visual inspection by trained raters, using the Actilife sleep analysis tab with the input of self-reported in-bed and out-of-bed times from participant sleep logs. After in-bed and out-of-bed time is determined by coder visual inspection, the Cole-Kripke algorithm [51] will be used to assess minute by minute sleep versus wake state. Variables include daily sleep duration, sleep onset time, sleep offset time, sleep efficiency, and minutes awake after sleep onset (WASO).

Objective measures of locations were obtained through participants wearing a Qstarz GPS device (BT-Q1000XT) attached to a belt worn on the waist. The device records data every 15 s. Missing data are imputed from a validated algorithm [52]. The GPS device logs geographic location coordinates, distance, speed, elevation, and time. The Qstarz has an industry reported accuracy of 3 m, and independent validation has shown that median error of the device varies by behavior (from 3.9 m for walking to 0.5 m for driving) and environment (from 5.2 m in urban canyons to 0.7 m in open areas) [53]. Participants were instructed to charge the GPS device overnight. The GPS data will be processed and joined to the accelerometer data using the Personal Activity and Location Measurement System (PALMS) [54]. Data will be aggregated and merged at the minute level. Indoor/outdoor locations will also be calculated using validated algorithms in PALMS [55]. The GPS device collects the signal to noise ratio of satellites in communication with the device. Higher ratios indicate more interference and likelihood of an indoor location. We have tested and validated a threshold of 250, which differentiates indoor and outdoor locations with over 85% accuracy compared to in person observations and coded images captures by person worn cameras.

Dietary measures were based on a 24-h multiple-pass food recall collected on 2 days by trained research staff using the NDSR (Nutrition Data System for Research) Software versions 2015 and 2016, a Windows-based program for food intake data entry and analysis developed by the Nutrition Coordinating Center at the University of Minnesota. The recalls were done on one weekday and one weekend day. Participants were given food portion visuals to aid in recall of portion sizes. NDSR allows research staff to collect a participant’s food intake for the previous day from midnight to midnight. The software guides the interviewer through its completion using a dynamic user interface. It is available in English and Spanish. A research staff member completed the master training course at the University of Minnesota on how to use the software and train others to administer the NDSR. Research staff participated in a rigorous training, and were assigned a set number of practices before completing the standardized test for certification. Ongoing monthly quality control checks of 10% of NDSRs were scheduled to maintain the quality of food interviews and data entry. Quality checks and staff feedback were conducted by the master trainer. All micro- and macronutrients are obtained, as well as data on foods and food groups. Reports per participant from NDSR will be used for primary analyses, and will include information on total calories, fat calories, fiber, macronutrients, and fruits and vegetables. Dietary outcomes from NDSR data include total calories, fat calories, fiber, and fruit and vegetable intake [56].

### Objective environmental exposures

The goal of the study is to better understand how environmental exposure to PA and diet-related environments impacts both behaviors and cancer-related biomarkers. Exposure in the study is measured in two ways: static measures around participants’ home and work locations, and dynamic measures using GPS traces of participants throughout the day. These two methods of measuring exposure will be compared to advance cancer exposure risk assessment. GIS data of the environment includes metrics of various land uses (retail, park, beaches, industrial, vacant), food outlet locations (grocery, fast food, restaurant, convenience store), walkability, recreation, public transportation, greenness, and crime. The data will be derived from the local government agency, SANDAG, as well as commercial data from Environmental Sciences Research Institute (ESRI) and Dun & Bradstreet.

Static measures of exposure are derived from buffers around participant homes as well as work places for those who work. The majority of studies that examine the relationship between environment and behaviors utilize a 400 m – 2 km buffer around a location to define an individual’s environment [34, 57]. A 1 km buffer around participants’ home and work locations will be created, and environmental variables contained in that buffer will be calculated for each participant. Static characterization of an individual’s environment does not accurately reflect a person’s daily mobility path and exposures that occur outside of the home and work environments, limiting the variance in environmental exposures over the study data collection period [58, 59]. Furthermore, single location estimates of exposure underestimate associations between environment and cancer risk factors when related to behaviors accumulated over the course of entire days, such as daily physical activity or total calories consumed [60, 61]. GPS devices offer a potential solution to these problems by providing a daily trace of an individual’s movement, which can be converted into a total dynamic exposure metric across the day. GPS-based dynamic measures of exposure will be calculated with the Kernel Density Equation (KDE) tool in ArcGIS. All GPS points for the entire participant’s wear time will be used to create a total exposure surface, which can then be multiplied by environmental variables to derive a total exposure measure that accounts for locations visited and the time spent in all locations [39].

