This paper describes the protocol of a cross-sectional study of objective measures of PA, sleep, and environments, high quality measures of dietary intake, and biomarkers in Hispanic and non-Hispanic adults. The study completed recruitment in October of 2017, and is now in analysis phase. In total, 602 adults aged 35–80 years old were recruited, with 40% of the sample being Hispanic. The primary objective of the Community of Mine study is to advance methods of cancer risk exposure assessment by measuring both neighborhood access and total exposure to healthy environments by integrating Global Positioning System (GPS) data with Geographical Information System (GIS) data across the full day. These measures of exposure are expected to be associated with breast and colon cancer risk factors assessed through biomarkers, as well as PA and diet behaviors measured through accelerometry and food recalls. We hypothesize that dynamic minute-level GPS based measures of environmental exposures will be more strongly related to behavior, as well as insulin and inflammation biomarkers than static environmental measures based on participants’ home and work address. Figure 1 shows the hypothesized relationships between environments, behaviors, and biomarkers.

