### Statistical approach

Our main objective is to compare Dynamic and Static GIS measures of PA and food environments and their associations with PA behaviors, BMI, diet, and biological markers. To test if the Dynamic GIS exposures are more strongly correlated with outcomes than the Static measures, we will apply the methods of Dunn and Clark [71] for dependent correlations (e.g., comparing two correlations which have a common variable, i.e., the PA behaviors or biomarkers). In addition, we will fit generalized estimating equations (GEE) models to examine associations between exposure to PA supportive environments (main effect) and outcomes (PA, BMI, diet, biomarkers) with adjustment for individual level confounding covariates (e.g. demographics, medication use for biomarker analyses), and block group clustering effects. We will use the multiple-informant approach developed by Horton et al. [72] to test if regression coefficients between PA and outcomes differ for the dynamic vs static GIS measures. We will examine interactions between covariates (e.g., ethnicity, age) and GIS measures on outcomes, to test if these factors moderate exposure-outcome associations. Similar analyses will be conducted for the self-reported outcomes, and Static versus Dynamic GIS measures of healthy eating promoting environments.

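### The static and dynamic exposures differ in spatial weighting as well as in mobility, so neither a difference nor a null result can be credited to mobility or GPS.

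*Protocol article*

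**What the plan says.** Under Objective environmental exposures, the protocol article fixes both measures. For the static one, the radius is set at 1 km and the rule reads "environmental variables contained in that buffer will be calculated for each participant". The centres are the home and work addresses, and no distance weighting inside the buffer is mentioned. For the dynamic one, "GPS-based dynamic measures of exposure will be calculated with the Kernel Density Equation (KDE) tool in ArcGIS". The resulting surface of all GPS points is then combined with the environmental layers into one total that reflects both the places visited and the time spent in them. The same section announces the contrast: "These two methods of measuring exposure will be compared to advance cancer exposure risk assessment".

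The Background gives the hypothesis: "We hypothesize that dynamic minute-level GPS based measures of environmental exposures will be more strongly related to behavior" and to the biomarkers than measures based on home and work address. The Statistical approach gives the test, "To test if the Dynamic GIS exposures are more strongly correlated with outcomes than the Static measures": the Dunn-Clark method for dependent correlations, with a multiple-informant comparison of regression coefficients alongside it.

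The reason offered for expecting the dynamic measure to do better is that static measures miss daily movement and time spent away from home and work. The Discussion goes further. It hopes the results will show that selecting participants by neighbourhood type may be unnecessary, because GPS data may supply enough exposure variability.

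**The concern.** Two things change at once between the measures. One is the set of places: home and work, or the whole GPS trace. The other is the spatial operator: everything within 1 km, or a kernel that gives more weight to what is close. The article describes neither a static measure using the kernel nor a GPS measure using the 1 km buffer, so nothing separates the two changes.

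The article itself reports that most studies use buffers from 400 m to 2 km, so the relevant scale is unsettled. If the kernel happens to sit nearer to that scale than the 1 km disc, the dynamic measure gains for a reason unrelated to mobility. If it sits further away, a real mobility gain can be hidden or reversed. At stake is the central claim of the study, and the practical inference in the Discussion about whether neighbourhood-based recruitment is needed.

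**Working it through.** **The plan's own figure.** From Sample size: correlations 0.32 (dynamic) and 0.15 (static) with the outcome, 0.2 between the measures, alpha 0.01 two-sided, 80% power. On the Fisher z scale,

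N = (z₀.₉₉₅ + z₀.₈₀)² (2 − 2s) / (atanh a − atanh b)² + 3,

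s = [c(1 − a² − b²) − ½ab(1 − a² − b² − c²)] / [(1 − a²)(1 − b²)].

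With a = 0.32, b = 0.15, c = 0.2: s = 0.1766, 2 − 2s = 1.647, and the z difference is 0.3316 − 0.1511 = 0.1805. So N = (2.576 + 0.842)² × 1.647 / 0.1805² + 3 ≈ 593. The article states 648, which this does not reproduce. That is a separate matter and does not affect the present point; the formula is used below at the achieved n = 602.

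**What the dynamic measure becomes without mobility.** If the product of surface and layer is summed over cells, the dynamic exposure is the average, over GPS points, of the kernel-weighted environment around each point. If every point is at home, it is the kernel-weighted environment around home. The static measure is then the 1 km disc around the same point. Mobility contributes nothing, yet the two variables differ.

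**One case by hand.** Assume a quartic kernel of radius 500 m, an environment with exponential correlation of length 500 m, and an outcome driven by the kernel-weighted home environment. Kernel and disc then correlate c = 0.808.
- Outcome correlation 0.32: a = 0.320, b = 0.320 × 0.808 = 0.259. Then s = 0.7926, standard error = √(0.4148/599) = 0.0263, z difference = 0.0666, ratio = 2.53. The probability of favouring the dynamic measure is Φ(2.53 − 2.576) ≈ 0.48. A 4,000-replicate simulation gave 0.475.
- Outcome correlation 0.15: a = 0.150, b = 0.150 × 0.808 = 0.121. Then s = 0.8048, standard error = √(0.3904/599) = 0.0255, z difference = 0.0293, ratio = 1.15. The probability is Φ(1.15 − 2.576) ≈ 0.08.

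The nominal rate is 0.005 per side. If the outcome is driven by the flat 1 km disc instead, the rates are almost the same but favour the static measure.

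**Range.** No mobility, n = 602, alpha 0.01 two-sided, clustering ignored. Assumed: quartic kernel radius 200-1000 m, Gaussian environmental smoothing SD 250-1000 m, and an outcome tied to the mean within 400 m, 1 km or 2 km of home.

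| Correlation of outcome with correctly scaled home exposure | Favours kernel, true scale 400 m | Favours buffer, true scale 1-2 km |
|---|---|---|
| 0.15 (the article's static value) | about 1-23% | about 1-27% |
| 0.32 (the article's dynamic value) | about 1-93% | about 1-96% |

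Take smoothing SD 500 m and radius 400 m, with true scales of 400 m, 1 km and 2 km. At 0.15 the rates are about 2%, 3% and 27%; at 0.32 they are about 9%, 15% and 96%. In each triple the first figure favours the kernel and the other two favour the buffer.

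**With a matched kernel.** With the same kernel and radius on both sides, no mobility effect and 80 m of location jitter each way, total rejection was 0.8% to 1.1% (correlation 0.32), in line with the nominal 1%.

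**The case against.** The strongest reply is that the planned test answers the planned question. The hypothesis and objective compare two ways of measuring exposure, with the conventional buffer as the established method. For that comparison Dunn-Clark is valid. This stands.

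A reader might infer that the main test has an inflated type I error and should be replaced. The documents do not support that. In the illustrated cases the population correlations of the two measures with the outcome really differ, so rejecting their equality is correct. What fails is the step from the rejection to mobility. Nor do the largest figures show GPS being wrongly credited: the 27% and 96% in the example favour the buffer.

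Three further objections limit the size:
- A correlation of 0.32 for a home-only exposure is more than the article assumes for its static measure. At 0.15 the effect shrinks considerably.
- Zero mobility is an extreme case; the age range was chosen partly to include employed adults likely to spend time away from home. The illustration does not say how much of an observed difference weighting would explain.
- Kernel radius, environmental smoothness and true scale are not in the article, and the absence of weighting in the buffer is inferred. In a smooth environment with a true scale of 1 km or less, the excess is only about 1-2%.

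A condensed article may leave the bandwidth and sensitivity analyses to a fuller plan that is not shown, so the missing bandwidth is not the complaint. The use of two different operators is stated, and a kernel is not a flat disc at any bandwidth.

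**Conclusion.** The point holds as one of attribution. The article pairs a 1 km home and work buffer with a kernel-density surface, and credits any gain to mobility and GPS data. The planned tests can show which package relates more strongly to an outcome. They cannot show that mobility is the reason, and a null result does not show that mobility adds nothing.

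How much this matters ranges from negligible to large, depending on quantities the article does not give. With nobody moving, the favoured direction is declared in about 1% to about a quarter of studies at an outcome correlation of 0.15, and in up to more than nine in ten at 0.32, against 0.5% nominal. These figures rest on the assumed kernel shape and radii, smoothness and true scales, and they ignore clustering. The direction can go either way.

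**What to change.** Keep the 1 km buffer comparison as the main test; it answers the stated question and allows comparison with earlier studies. Before the outcome analyses, prespecify a sensitivity analysis with a matched static measure: the same KDE tool, search radius and cell size, run on the home and work coordinates and weighted by time at each. State the source of the time weights. If they come from GPS, the matched pair isolates places visited beyond home and work, and not the split of time between the two. Apply the same Dunn-Clark and multiple-informant tests to this pair. Let any statement that mobility or GPS adds information, including the inference about neighbourhood-based recruitment, rest on it.

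The cost is some further GIS runs on coordinates already held and one more static measure to compute and report. No new data are needed.

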### Study procedure

Once eligibility criteria were confirmed and the signed consent form was received, participants were scheduled for a clinical visit. A packet with devices, wear instructions, and instructions for the visit were delivered to participants approximately 1 week prior to the scheduled visit time. Participants were asked to wear an accelerometer on both the hip and wrist and a GPS device on a belt with the hip accelerometer for 14 days, with a minimum of 10 h of wear time per day. Writs accelerometers were requested to be worn at all times including during sleep. They were asked to complete a sleep log for each night. Participants were asked to fast for 12 h prior to the visit for a 45 mL blood draw and urine (~ 50 mL) sample. At the visit, blood pressure, height, weight, hip and waist circumference, temperature, and respiratory rate were recorded. Blood and urine samples were held on ice (EDTA tubes for 60 minutes, urine samples for 60 minutes, serum tubes for 30 minutes after 30 minutes at room temp to allow clotting) before centrifugation and aliquoting. Plasma, serum, and buffy coat from blood drawn into EDTA and serum tubes was isolated by centrifugation at 4 °C, then aliquoted and stored at − 80 °C. Urine samples were aliquoted and stored at − 80 °C.

During the clinical visit, participants completed a medical history interview that includes any current medications. Demographic characteristics (e.g., age, gender, race/ethnicity) were collected via self-report survey. Standard surveys measured health conditions, depressive symptoms, quality of life, sleep quality, fear of falling, and neighborhood perceptions. Participants received new devices at the clinic visit due to memory limitations on the devices. They were instructed to mail the devices back and, if at the end of the study they did not have at least 7 days of data, they were asked to re-wear the devices. Participants completed two 24-h dietary recall assessments (one weekday, one weekend). One dietary assessment was completed at the visit and the other was scheduled over the phone a few days after the visit. Participants received reminder calls to wear the devices and to allow them to ask questions. Once devices were returned participants were paid $100 for their participation. Participants also received $25 the day of their clinical visit to cover travel expenses and parking is provided.

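### For device-measured physical activity and walking, the dynamic exposure contains the outcome's own minutes and the static buffer cannot, so the dynamic-versus-static test leans toward the hypothesis for place-type layers

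*Protocol article*

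**What the plan says.** The rule for dynamic exposure is in the protocol article under Objective environmental exposures: "All GPS points for the entire participant’s wear time will be used to create a total exposure surface". The surface is then multiplied by environmental variables to "derive a total exposure measure that accounts for locations visited and the time spent in all locations". The static comparator is fixed by address: "A 1 km buffer around participants’ home and work locations will be created". The layers listed in the same section include "metrics of various land uses (retail, park, beaches, industrial, vacant), food outlet locations (grocery, fast food, restaurant, convenience store), walkability, recreation".

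Study procedure has participants wear "a GPS device on a belt with the hip accelerometer for 14 days". Under Behavioral outcomes, the GPS and accelerometer streams are joined ("Data will be aggregated and merged at the minute level"), and the activity outcome comes from that accelerometer: "The hip worn PA variables are created from collected accelerometer data employing traditional accelerometer count per minute (cpm) cut offs". Walking/running is also classified by a random forest.

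The Background section hypothesizes that "dynamic minute-level GPS based measures of environmental exposures will be more strongly related to behavior", and extends this to insulin and inflammation biomarkers. Statistical approach tests it with Dunn and Clark's method for two correlations that share the outcome.

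**The concern.** The two exposures do not stand in the same relation to the activity outcome. A minute of walking in a park adds one minute to walking and one GPS-weighted minute to dynamic park exposure. It adds nothing to the home or work buffer. A person who chooses to exercise in a measured place thus raises their own dynamic exposure by the act being predicted. This happens whether or not the place has any influence on how active they are.

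Only the dynamic correlation is raised, and the test is of the difference between the dynamic and static correlations. For activity outcomes, a positive result could not separate better exposure measurement from shared minutes.

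Nothing in the article deals with this. The self-selection survey (Self-report measures and covariates) asks why people moved to a neighborhood, not why they visit places during the day. Covariate adjustment in the GEE models does not remove shared minutes. The Discussion gives only the general cross-sectional limitation.

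**Working it through.** **1. The plan's own figure.** Inputs from Sample size: correlations 0.32 (dynamic) and 0.15 (static), static–dynamic correlation 0.2, two-sided α = 0.01, 80% power, stated n = 648.

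- c = [0.2(1 − 0.32² − 0.15²) − 0.5·0.32·0.15·(1 − 0.32² − 0.15² − 0.2²)] / [(1 − 0.32²)(1 − 0.15²)] = 0.177
- n = (2.576 + 0.842)² · 2(1 − 0.177) / (0.3316 − 0.1511)² + 3 = 594

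This does not reproduce 648, but that is a separate matter with no bearing here. On these inputs, before clustering, power at the achieved 602 is about 81%. What matters below is the planned contrast: 0.32 − 0.15 = 0.17.

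**2. Correlation induced by shared minutes.** The article does not say how much activity falls in any layer, so everything from here on is an illustration under stated assumptions. Let A be MVPA minutes per day, N non-active minutes in the layer, and p the person's share of MVPA done there (mean s, independent of A). Environment has no effect on A. The exposure is X = N + pA, so

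r(A, X) = s·SD(A) / SD(X).

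Assumptions: A is gamma with mean 35 and SD 24.75 min. N is exponential with base scale 10, 20 or 40 min, multiplied by exp(0.3W), where W is the static home score. p is Beta(1, (1 − s)/s).

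Worked cell, s = 0.20 and base 10:

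- Var(N) = 100(2e^0.18 − e^0.09) = 130.0
- Var(pA) = 0.0667·1837.5 − 0.04·1225 = 73.5
- SD(X) = √203.5 = 14.27
- r = 0.20·24.75/14.27 = 0.347

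With static r = 0 and static–dynamic correlation 0.22, Z = atanh(0.347)·√(599/(2·0.78)) = 7.1 against a critical value of 2.576.

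Simulation at n = 602 (nominal rate in the dynamic direction 0.5%):

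| s | Base scale of N (min) | r by formula | r simulated | Declared stronger, all points | Declared stronger, activity minutes removed |
|---|---|---|---|---|---|
| 0.05 | 40 | 0.027 | 0.027 | 2.7% | 0.7% |
| 0.10 | 20 | 0.106 | 0.107 | 35% | 0.5% |
| 0.10 | 10 | 0.201 | 0.202 | 92% | 0.4% |
| 0.20 | 40 | 0.107 | 0.110 | 39% | 0.9% |
| 0.20 | 10 | 0.347 | 0.346 | 100% | 0.5% |
| 0.40 | 10 | 0.526 | 0.524 | 100% | 0.2% |

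**3. Sensitivity to spread.** Same structure with lognormal inputs: median MVPA 20 min, share 20–30%, static–dynamic correlation 0.2.

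- Background median 15–30 min, log-SD 0.8 for both: r = 0.13 to 0.37, declared stronger in 52% to >99%. At share 0.3 and background 15: r = 0.3·26.08/√(19.56² + 7.82²) = 0.371.
- Background median 15–30 min, log-SD 1.0 for background and 0.6 for MVPA: r = 0.05 to 0.145, 5–60%.
- Background median 60–120 min, log-SD 0.8 for both: r = 0.03 to 0.10, 3–27%.

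**4. Score-type layers.** Here exposure is a time-weighted mean score over 840 min of wear, with 50% or 100% of MVPA in places scoring 0 to 5 SD above other places.

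- No difference in score: r about 0.00, declared stronger in about 0.5%, so there is no artefact.
- 1 SD higher: r = 0.02 to 0.04, 6–28%.
- 5 SD higher, all MVPA there: r = 0.18, 100%.

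Static and dynamic correlate at about 0.9 in this model, so even small differences are detectable. Removing activity minutes returns the rate to 0.1–1.1%.

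**The case against.** Four points on the other side deserve weight.

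*The planned exposure is a kernel-density surface, not minutes in one feature.* With at least 10 h of wear requested, 4–6 active minutes in a feature are 0.7–1% of the points. This stands as a reason for caution over diffuse layers such as walkability, greenness or crime. It does not dispose of place-type layers: the induced correlation depends on the share of between-person variance, s·SD(A)/SD(X), not on the share of points.

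*Total exposure over the day is the stated target.* Walking in a walkable place is part of that exposure and of the hypothesized pathway. This stands, and it bears on the remedy. In an illustration where time in a feature truly drives walking there, filtering cut r from 0.68 to 0.37 (on average 60% of that time active), and from 0.57 to 0.13 (active share uniform from 0 to 1). A reader might infer that the filtered surface should replace the all-points surface. That would exchange one bias for another.

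*Diet.* A reader might infer that visiting an outlet to eat has the same effect on food exposure and diet. The documents do not support this. Diet comes from two 24-hour recalls and shares no minute with the GPS trace. What remains is ordinary reverse causation.

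*Reach.* Insulin resistance and inflammation, the primary biomarker outcomes, and BMI also share no minutes with the trace. The problem concerns one outcome family.

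**Conclusion.** The point holds for device-measured activity and walking against place-type layers. The article fixes the rule, the rule puts outcome minutes into one comparator only, and the direction favors the hypothesis.

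The size cannot be settled from the documents. At n = 602 with no environmental effect it is negligible (about 1–3% declared stronger) for a diffuse layer whose activity places score no higher than others, or where little activity falls in the layer and background time there is long. At the other end rejection is almost certain: r about 0.37 and >99% in the lognormal illustration, and larger still in the most extreme cell of the table. Such values can match or exceed the planned difference of 0.17. All of these figures rest on assumed MVPA levels, shares and background times.

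A reader might infer that a dynamic advantage for activity would be wholly an artefact, or that a false positive is more likely than not. Neither follows. Fuller capture of exposure may raise the dynamic correlation legitimately, and rates above 50% arise under only some of the assumptions. Nor does the point undermine the comparison for diet, BMI or biomarkers.

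**What to change.** For activity and walking outcomes, compute a second dynamic surface that omits GPS minutes classed as the outcome activity, and run the same Dunn and Clark test on it. Report it beside the all-points version. An alternative is to take exposure and outcome from different days of the wear period. That removes the shared minutes but not habitual use of the same places, so it is the weaker check.

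Claim that dynamic exposure is more strongly related to physical activity only if the result holds in both versions. State selective daily mobility as a limitation. Leave the diet, BMI and biomarker comparisons as planned.

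The computing cost is low: the streams are merged by minute, activity is already classified, and the study is only now entering analysis. The real cost is inferential. The filtered version drops genuine exposure during activity and can understate a true association, possibly by a large amount. A result that holds only with all points should therefore be reported as unresolved, not as refuted.
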